### Study Population

The study includes patients operated for a distal radius or ankle fracture at a Level 1 trauma center in Switzerland. Patients presenting with these fractures at the emergency department will be eligible for study inclusion if they fulfill all of the following criteria: indication for an operation of a distal radius fracture, according to the Arbeitsgemeinschaft für Osteosynthesefragen (AO) Classification types 23-A-C [4], or an ankle (according to the AO Classification Types 44-A-C) fracture, 18 years of age or older, sufficient understanding and writing of German language, and signed informed consent. The informed consent forms will be stored by the study nurse during the trial.

Patients are excluded if they meet at least one of the following exclusion criteria: not willing/able to sign the informed consent, indication for postoperative computed tomography (CT), pathological fractures, open fractures (>grade I according to Anderson and Gustilo [11]), patients not able to attend the 6 weeks outpatient control, or missed intraoperative standardized radiographs.

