#### Inclusion Period

After sufficient information is provided to all trauma surgeons, inclusion starts. Intraoperative radiographs are obtained by the ZIEHM SOLO (Ziehm Imaging GmbH). These radiographs are saved separately in our PACS. The next day, these radiographs are evaluated by the senior surgeon of the department of orthopedics and trauma surgery and a senior radiologist. If the quality of the intraoperative radiographs is standardized and good, the patient remains in the study arm to which they were assigned.

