### Randomization

Prior to the operation, the patients are randomized to the control or the intervention group. The randomization will be carried out using a special in-hospital randomization tool. Thereafter, the patient will be included in one of the following two groups.

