#### Intervention Group (Group II)

Patients belonging to the intervention group will have a modified postoperative protocol. After interdisciplinary consensus (between the head of the orthopedics department and trauma surgery and radiology) that the quality of the intraoperative radiographs are performed in a standardized fashion with good quality and that the reposition is within the predefined standards, patients will be mobilized according to our routine postoperative protocol and will be reviewed in our outpatient department after 6 weeks (clinically and radiologically).

If the quality of the intraoperative radiographs or the reduction is not acceptable, additional imaging (plain radiographs or CT) or a revision operation is performed.

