#### Primary Outcome

We defined the primary outcome as any re-intervention or necessity for additional imaging due to insufficient intraoperative imaging or achieved reduction.

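### Patients are randomized before surgery, but missing or inadequate intraoperative views can remove them afterwards, and the same failure is a named cause of the primary outcome

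*Protocol article*

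**What the plan says.** All places are in the Methods of the protocol article.

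- **Randomization:** "Prior to the operation, the patients are randomized to the control or the intervention group".
- **Study Population:** the exclusion list ends with "patients not able to attend the 6 weeks outpatient control, or missed intraoperative standardized radiographs". The last item can only be met during or after the operation.
- **Inclusion Period:** "The next day, these radiographs are evaluated by the senior surgeon of the department of orthopedics and trauma surgery and a senior radiologist". Then: "If the quality of the intraoperative radiographs is standardized and good, the patient remains in the study arm to which they were assigned". The section does not say what happens to other patients.
- **Intervention Group (Group II):** "If the quality of the intraoperative radiographs or the reduction is not acceptable, additional imaging (plain radiographs or CT) or a revision operation is performed".
- **Primary Outcome:** "any re-intervention or necessity for additional imaging due to insufficient intraoperative imaging or achieved reduction".

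The Hypothesis section limits the question to patients in whom adequate standardized intraoperative images were obtained. The title and Strengths and Limitations describe the trial as open label and unblinded.

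**The concern.** Image adequacy is known only after allocation, and it is used in two ways. It decides who stays in the trial (Study Population and, by implication, Inclusion Period). It also triggers further imaging or revision in Group II and is one of the two causes named in the primary outcome. Removing randomized patients on that criterion is selection on a component of the outcome, made by people who can know the arm.

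The arms are not affected alike. A control receives the day-1 film whatever the C-arm images look like. In Group II, inadequate images themselves lead to the additional imaging or revision that the outcome counts. A Group II patient without adequate views could thus be dropped under one section and counted as an event under another. The noninferiority conclusion could depend on which section the analyst follows.

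**Working it through.** **1. Order of events.** Randomization, then surgery, then image review the next day. Any exclusion for missing or inadequate intraoperative views is therefore made after randomization.

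**2. The sections side by side, for a Group II patient without adequate views.**

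| Section | Consequence |
|---|---|
| Study Population | excluded, if the views were missed |
| Inclusion Period | not confirmed as staying in the arm; departure implied, not written |
| Intervention Group | further imaging or revision, on the Group II pathway |
| Primary Outcome | further imaging or re-intervention for this cause is an event |

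The explicit conflict is between the first row and the last. The second row adds to it by implication.

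**3. The plan's own sample size.** No margin is printed, so 158 per arm cannot be reproduced from the stated inputs alone. Solving for the margin at 7.2% in both arms, 80% power and one-sided 0.05:

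d = (1.645 + 0.842) × √(2 × 0.072 × 0.928 / 158) = 0.0723, or about 7.2 points.

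At one-sided 0.025 the implied margin would be about 8.15 points. The inflated figure reproduces: 158 × 1.05 = 165.9, or 166 per arm.

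**4. Illustration.** From the article: 7.2% and 166 per arm. Assumed:

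- a margin of 0.0723;
- a share f of inadequate images, equal in both arms (no figure is given);
- every inadequate image in Group II counted as an event;
- an event rate c among poor-image controls (no figure is given);
- no loss to follow-up.

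If removed: 166 × (1 − f) per arm, with 7.2% in both. If kept: 166 per arm, with

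- Group II rate = f + (1 − f) × 0.072
- Group I rate = f × c + (1 − f) × 0.072

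For f = 0.05 the Group II rate is 0.05 + 0.95 × 0.072 = 11.8%. With c = 0.50 the Group I rate is 0.025 + 0.0684 = 9.3%.

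The chance of declaring noninferiority is the probability, for independent binomial counts, that the Wald upper one-sided 95% limit of the difference lies below 0.0723:

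| Inadequate, f | Group II rate if kept | Removed | Kept, c = 7.2% | Kept, c = 50% | Kept, c = 100% |
|---|---|---|---|---|---|
| 3% | 10.0% | 81% | 43% | 57% | 72% |
| 5% | 11.8% | 79% | 21% | 42% | 66% |
| 10% | 16.5% | 78% | 1.5% | 15% | 56% |
| 20% | 25.8% | 75% | 0% | 1% | 45% |

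**5. Reading the table.** At c = 7.2% or 50% the true rates differ between the arms, and removal hides the difference. At c = 100% both arms have the same true rate, so the lower figures reflect only the larger variance at a higher event rate. The column c = 7.2% is the worst case.

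**The case against.** **The departure is partly inferred.** Inclusion Period gives only the positive condition. The Group II section can be read as its missing other branch, in which case those two sections and the outcome definition agree. This stands. A missed view may also mean one not obtained rather than one of poor quality. Even so, a view not obtained is insufficient intraoperative imaging, so the exclusion still overlaps with the outcome.

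**Restriction to adequate images is the stated hypothesis.** True, and the restricted analysis should be kept. The difficulty is restricting after randomization while the outcome counts the failure that defines the restriction. Randomizing after the image review would preserve the conditional question for patients still to be enrolled, but would not settle the 104 already enrolled.

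**Analysis sets belong in an analysis plan.** Not stating one in an article is no fault. The point here is that an exclusion and an outcome definition, both printed, disagree.

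**Stronger readings that the article does not support.** A reader might infer that removal necessarily favours omitting the film. It need not: removing poor-image controls can also take events out of Group I. A reader might infer unequal removal because Inclusion Period names a senior surgeon and a senior radiologist while the Group II section names department heads. These may be the same people. Nor does any text say that an enrolled patient has been removed, or that the day-1 film is used to judge the C-arm images.

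**Conclusion.** The point holds as an inconsistency in the printed rules. An exclusion that can only be met after randomization, and by implication a next-day retention rule, can remove patients on a criterion that is part of the primary outcome. If they are followed as written, the comparison is not between the groups as randomized.

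The net direction and size of bias cannot be fixed, because the article gives neither the share of inadequate images nor the event rate among controls who have them. Under the assumptions shown, with 3% to 20% inadequate, removal leaves the chance of declaring noninferiority at 75% to 81%. Keeping the patients gives anything from 0% to 72%. The implementation training may keep the share near the low end. Even at 3%, the figure is 81% if removed and 43% to 72% if kept, so the choice of section matters to the primary conclusion and should be settled before analysis.

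**What to change.** Reconcile Study Population, Inclusion Period, Randomization, Intervention Group and Primary Outcome to a single disposition for randomized patients with missing or inadequate intraoperative views:

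1. No randomized patient leaves the assigned arm, follow-up or analysis for this reason. The exclusion for missed views no longer applies once a patient is randomized.
2. Analyse all randomized patients in the arm assigned.
3. Answer the conditional hypothesis in an accompanying analysis of patients with adequate images. Rate adequacy by the same criteria in both arms, from the stored C-arm images, without the arm label.
4. Report the share failing by arm, and retain the data of any patient already removed.

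This concerns who is followed and analysed. It takes no position on when further imaging or revision is indicated.

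The cost is amended wording and a second analysis set, plus rating the stored images without the arm label; no extra visits are needed. The drawback is that patients with poor images dilute the all-randomized result, which is why both analyses are reported.

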### Randomization

Prior to the operation, the patients are randomized to the control or the intervention group. The randomization will be carried out using a special in-hospital randomization tool. Thereafter, the patient will be included in one of the following two groups.

#### Control Group (Group I)

Patients belonging to the control group will be treated according to our current protocol, including a standardized postoperative radiograph. Regular postoperative radiographs are performed in the department of radiology and contain an anterior-posterior and lateral tilted view of the wrist. In patients with an ankle fracture, a lateral view and a mortise view are obtained. Generally, patients operated on for a distal radius fracture will have a functional after treatment and will be restricted in weight bearing for the first 6 weeks postoperative. Operatively treated ankle fractures will generally receive a functional after treatment with weight bearing restricted to 15 kg for 6 weeks. All patients will have a clinical and radiological outpatient control after 6 weeks.

#### Intervention Group (Group II)

Patients belonging to the intervention group will have a modified postoperative protocol. After interdisciplinary consensus (between the head of the orthopedics department and trauma surgery and radiology) that the quality of the intraoperative radiographs are performed in a standardized fashion with good quality and that the reposition is within the predefined standards, patients will be mobilized according to our routine postoperative protocol and will be reviewed in our outpatient department after 6 weeks (clinically and radiologically).

If the quality of the intraoperative radiographs or the reduction is not acceptable, additional imaging (plain radiographs or CT) or a revision operation is performed.

### Outcome

As we present a noninferiority approach, the purpose of this analysis is to show comparable results in the intervention group in terms of functional outcome and safety for the patients.

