### Statistical Analysis

Statistical analysis will be carried out using SPSS, IBM Version 21. In order to answer the primary research questions, the number of re-interventions will be compared between both groups. Additionally, we will use regression *models* to try to identify risk factors for these re-interventions such as timing and duration of surgery and the experience of the surgeon.

In order to address the secondary research questions, the evaluated specific and nonspecific outcome scores will be compared between the two groups using means and standard deviation.

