### Sample Size Calculation

We determined the sample size for both the radius and ankle fracture group after a retrospective evaluation concerning the rate of postoperative treatment plan changes. We found a rate of 7.2% changes in treatment plan after obtaining standard postoperative radiographs in 2014. Based on these findings and using a power of 0.80 and alpha failure of .05, we performed a sample size calculation.

Based on a noninferiority approach, we calculated 158 patients needed in each treatment arm. Corresponding to the standard protocol following operative fracture care, we have a standard first outpatient control after 6 weeks. Based on a separate evaluation, concerning the frequency of patients being lost to follow-up, 4.6% of our patients in 2014 did not obtain their 6-week control. Therefore we added 5% loss of follow-up to our power calculation, resulting in 158 x 1.05=166 patients in each treatment arm.

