### Strengths and Limitations

This randomized trial will provide prospective data for a common health care problem and the appropriate aftercare. Due to its randomized design, this trial will provide high-quality evidence with clearly predefined objective results.

Outpatient control, for all patients 6 weeks postoperatively, performed by a specialized (orthopedic) trauma surgeon ensures comparable and objective analysis in terms of early surgical outcome.

As a secondary outcome measurement, functional analysis using validated questionnaires will provide additional information. If this trial demonstrates comparability in terms of quality in aftercare between both groups, this could be the basis for a change in standard postoperative process with savings in radiation exposure and health care costs.

Limitations of this study are the single-center design and the lack of blinding during the study period.

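### The trial is planned as noninferiority, but no margin or criterion for comparability is stated: the analysis is a plain group comparison, and 158 per arm rests on an unstated margin

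*Protocol article*

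**What the plan says.** The Abstract, Methods, Outcome and Sample Size Calculation sections all describe a noninferiority design. The Outcome section gives its aim: "the purpose of this analysis is to show comparable results in the intervention group in terms of functional outcome and safety for the patients".

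The Primary Outcome section defines the endpoint as "any re-intervention or necessity for additional imaging due to insufficient intraoperative imaging or achieved reduction". The Abstract likewise counts additional imaging as well as reoperation. For the primary question, however, the Statistical Analysis section says "the number of re-interventions will be compared between both groups". For function it says that the specific and nonspecific scores "will be compared between the two groups using means and standard deviation".

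The Sample Size Calculation section reports "We found a rate of 7.2% changes in treatment plan after obtaining standard postoperative radiographs in 2014" and, "using a power of 0.80 and alpha failure of .05", arrives at 158 per arm, raised to 166 for loss to follow-up. It gives no margin, no sidedness for alpha and no expected rate in the intervention arm.

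Strengths and Limitations looks ahead to a change in standard practice: "If this trial demonstrates comparability in terms of quality in aftercare between both groups".

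**The concern.** A noninferiority conclusion needs a margin and a rule that sets the uncertainty of the estimate against it. The article has neither, for the primary outcome or for function. Finding no difference between groups does not show that omitting the radiograph is acceptable, because a small or noisy trial finds no difference easily. The error that matters here is to call omission acceptable when it doubles the event rate, and nothing stated controls that error.

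Two mismatches add to this. Function is named as something the noninferiority approach must show, yet it is a secondary outcome with no margin and no sample size. The analysis also counts re-interventions only, whereas the primary outcome and the 7.2% planning rate (see Rationale) include additional imaging.

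**Working it through.** **Inputs from the article.** Control rate p = 0.072; alpha 0.05 (sidedness not given); power 0.80; 158 evaluable per arm.

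**Assumptions.** Equal true rates in both arms for the sample size formula. The margin m is back-solved because none is stated.

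**1. The planned sample size.** For noninferiority of two proportions, n per arm = (z₁₋α + z₀.₈₀)² × 2p(1−p) / m², with 2p(1−p) = 2 × 0.072 × 0.928 = 0.1336.
- One-sided 0.05: (1.645 + 0.842)² × 0.1336 = 0.826. Setting n = 158 gives m = √(0.826/158) = 0.0723. A margin of exactly 7.2 points gives 0.826/0.072² = 159.4, so 160.
- One-sided 0.025: (1.960 + 0.842)² × 0.1336 = 1.049. Setting n = 158 gives m = √(1.049/158) = 0.0815.

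These margins tolerate an intervention rate of about 7.2 + 7.2 = 14.4% or 7.2 + 8.15 = 15.35%, that is 2.0 or 2.1 times the control rate. The figure of 158 does not identify the margin: a two-sided superiority calculation of 7.2% against 1.0% also gives 160. The follow-up step does reproduce: 158 × 1.05 = 165.9, so 166, and 2 × 166 = 332.

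**2. A plain comparison when events truly double (7.2% v 14.4%, 158 per arm).** The pooled rate is 0.108.
- SE under the null = √(2 × 0.108 × 0.892/158) = 0.0349.
- SE under the alternative = √((0.072 × 0.928 + 0.144 × 0.856)/158) = 0.0347.
- Power of a two-sided 0.05 test = Φ((0.072 − 1.96 × 0.0349)/0.0347) = 0.54.

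Exact binomial enumeration gives 0.551 for chi-square and 0.476 for Fisher. A true doubling is therefore non-significant in 45% (chi-square) or 52% (Fisher) of trials.

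**3. A confidence-limit rule on the same data.** Noninferiority is concluded if d + z₁₋α × SE(d) < m, where d is the observed rate in the intervention arm minus that in the control arm. The calculation uses the Wald SE, exact enumeration and m = 7.2 points.

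| True rates | One-sided 0.05 | One-sided 0.025 |
|---|---|---|
| 7.2% v 14.4% (harm equal to the margin) | passes 5.4% | passes 3.0% |
| 7.2% v 7.2% | passes 79% | passes 71% |

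A doubling lies exactly on the 7.2-point margin, so the pass rate is close to the nominal alpha by construction. At one-sided 0.025 a 7.2-point margin would need 1.049/0.072² = 202.3, so 203 per arm, which is why power drops to 71%. With the 8.15-point margin that fits 158 at that level, a doubling passes with probability about Φ((0.0815 − 0.072)/0.0347 − 1.96) = Φ(−1.69), or roughly 5%.

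**4. Counting re-interventions alone.** The article gives no rate for these, so the range is assumed. At 3.6% v 7.2% a plain two-sided comparison has 21% to 29% power, and at 2% v 4% it has 10% to 18%. A 7.2-point margin would also be too loose for the narrower count: a doubling from 2% to 4% would pass the rule in step 3 in 77% to 84% of trials. The margin and the endpoint have to be fixed together.

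**The case against.** The strongest reply is that the article names no significance test. To compare is a neutral word that a confidence interval would also satisfy, and the sentence in Strengths and Limitations is conditional. A reader might infer that the investigators plan to treat a non-significant result as proof of comparability, but the documents do not say so. The 45% describes what that reading would cost; it is not the error rate of a stated rule. It is also fair that the interval method and the analysis sets may sit in an analysis plan that is not shown, and their absence is not held against the article. The margin is different: it is an input to the sample size the article itself reports.

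A reader might also infer that a moderate loss of function would often go unnoticed. The documents do not support this. They give no standard deviation, no margin and no split between wrist and ankle fractures. With an assumed even split (79 per arm), a 0.3 SD loss in a fracture-specific score would be missed 53% of the time, but a 0.5 SD loss only 12%. The SF-36 and the pain scale are collected in all patients, where the figures at 158 per arm are 24% and under 1%. Secondary outcomes commonly have no sample size of their own, and questionnaires specific to each fracture are appropriate. What stands is that function was placed under the noninferiority purpose.

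Nor should smaller rises in events be counted as errors. A rise from 7.2% to 10.8% is 3.6 points, inside either back-solved margin, so concluding noninferiority there would not be a false claim.

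**Conclusion.** The concern holds in this form and needs correction before the results are analysed. As written, the plan has no criterion that could support its noninferiority conclusion, and its sample size depends on a margin and a sidedness that the reader cannot see. Read as no significant difference, a true doubling of events would pass 45% of the time by chi-square. Under a margin-based rule with the same 158 per arm it would pass about 3% to 5% of the time.

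These figures rest on the 7.2% control rate, on a margin back-solved rather than stated, and on a two-sided chi-square test that the article does not name. The absence of a criterion, the placing of function under the noninferiority purpose, and the mismatch between the defined and the analysed primary outcome follow from the text alone.

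**What to change.** 1. In Sample Size Calculation, state the noninferiority margin, its justification, and the sidedness of alpha that gave 158.
2. In Statistical Analysis, analyse the primary outcome as the Primary Outcome section defines it (re-intervention or additional imaging). Conclude noninferiority only if the upper confidence limit for the risk difference, intervention minus control, at the stated sidedness, lies below the margin. Say that a non-significant difference is not evidence of comparability.
3. For function, report mean differences with 95% confidence intervals as supportive and remove functional outcome from the noninferiority purpose in the Outcome section. Alternatively, pre-state a margin for each score.

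**Cost.** This is mainly a change of wording and analysis. The article reports 104 of 332 patients enrolled, so it could be made before the results are known. If the margin is the one implied by 158, no patients are added. If only a tighter margin can be justified, the size rises: 5 points would need 0.826/0.05² = 331 per arm at one-sided 0.05, or 1.049/0.05² = 420 at one-sided 0.025. The other cost is that the trial may end inconclusive where a plain comparison would have been called comparable.
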